### Pilates exercises

The exercises are shown in Additional file 1. The exercise sequences were divided in different ways to make the training more varied and to avoid dropouts (Additional file 2). The exercise schedule was produced by us based on an extensive bibliographical survey of Pilates exercises and their progression. We considered the degree of difficulty of each exercise as well as the dependence between volume and intensity.

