### Primary outcome

Quantification of the internal training load was evaluated in each training session with the three monitoring tools: SPE [6], HR [18], and HRV [18]. For the monitoring to be considered successful, two of the three monitoring tools must yield significant results. In addition, the correlation between SPE and HR should be moderate to high so that they can be used in clinical practice as low cost and easily applicable tools.

The SPE consists of a scale proposed by Borg where the participants choose the descriptor and number that best represents their psychophysiological stress in the training session [6]. It is a scale from 6 to 20 points, where 6 means “no effort” and 20 means “maximum effort.” To avoid biased responses, the question was standardized as: “From 6 to 20 points, how do you rate your perception of effort now?” All responses were recorded in individual records. The participants had previously been made familiar with the scale [6].

Prior to the sessions, participants were told how to estimate their SPE. It was explained to them that during the exercises it was necessary to perceive how much effort they were using so that every 5 minutes during a session they could estimate the SPE according to their individual perception for how exhausting the exercises were.

In addition, 15 min after the end of each session, the participants estimated the SPE again [6]. This final SPE was multiplied by the duration of the session in minutes, and the product represents the internal load in arbitrary units. The intensity of the session was classified into three zones according to the Borg scale used by Moreira et al. [19].

Quantification of the internal load training using the HR was performed using the TRIMP method. This evaluates the volume and intensity of the session through specific scores in each training zone, as proposed by Edwards [18, 20].

In addition to these methods for monitoring the training load, HRV was analyzed. The weekly mean of rMSSD (rMSSDmean) expressed in milliseconds and the weekly intra-individual coefficient of variation of rMSSD (rMSSDcv) expressed as a percentage will be used [21, 22]. These indices will be transformed to logarithms to mitigate outliers and simplify the analysis.

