### Statistical analysis

Descriptive statistics will be used, and the results presented as means, errors, standard deviations, percentages, and absolute numbers. The normality of the data will be evaluated through a Shapiro–Wilk test. In the comparison of the population profile and the cardiorespiratory, autonomic, and psychometric measures in the initial and final evaluations, the paired *t* test will be used for normal data or the Wilcoxon test for non-normal data. In the comparison between the groups, the unpaired *t* test or Mann–Whitney test will be used depending on the normality of the data, with the significance level set at *p* < 0.05. Differences based on magnitudes (Δ = final value – initial value) will also be calculated [35, 36] to verify the differences between the initial and final time points.

To analyze weekly differences in training loads using the SPE, HR, and HRV indices (ln rMSSDweekly and ln rMSSDcv) over the 12-week study duration, magnitude-based inferences will be calculated [36].

For ln rMSSDweekly, the smallest worthwhile change was set at 3% [37]. For SPE, HR, and ln rMSSDcv, the smallest worthwhile change is defined as 0.2 × between-subject standard deviation. The quantitative chances to find differences in the variables to be tested will be assessed qualitatively as follows: <1% almost certainly not, 1–5% very unlikely, 5–25% unlikely, 25–75% possible, 75–95% likely, 95–99% very likely, and >99% certain. If the chances of having higher and lower results are both >5%, the true difference was assessed as nuclear [35]. The magnitude of the effect size will be qualitatively interpreted using the following thresholds: <0.2 trivial, 0.2–0.6 small, 0.6–1.2 moderate, 1.2–2.0 large, 2.0–4.0 very large, and >4.0 nearly perfect [35].

To determine the correlations (dose–response) between ln rMSSD, HR, and SPE, Pearson’s or Spearman’s correlation will be used according to the normality of the data. The threshold used to evaluate the correlations quantitatively will be based on Hopkins [35] using the following criteria: <0.1 trivial, 0.1–0.3 small, 0.3–0.5 moderate, 0.5–0.7 large, 0.7–0.9 very large, and >0.9 almost perfect.

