The cutoff points for load increments with the HRV indices and SPE were obtained from the receiver operating characteristic curve. The sensitivity, specificity, positive predictive value, and negative predictive value for each level of the Pilates method will also be calculated. The area under the curve will be considered significant when values ≥0.65 are obtained [38]. In addition, a comparison will be made between the receiver operating characteristic curves of each HRV index to detect the most representative for determining the internal training load of the Pilates method.

The statistical analysis will be carried out with the *Statistical Package for the Social Sciences*, version 15.0 (SPSS Inc., Chicago, IL) and *MedCalc Software bvba*, version 14.10.2 (Oostende, Belgium). All data will be entered into the software twice. All participants included in the initial assessment will be considered under the intention-to-treat approach in which the worst outcome obtained by the study group will be selected to ensure the power of the data analysis.

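### The correlations labelled dose–response contain no planned dose, and the clinical-use criterion lets HR (or SPE) be endorsed through its correlation with the other tool alone

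*Protocol article*

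**What the plan says.** All references are to the protocol article.

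- **Statistical analysis, correlations:** the aim is given as "To determine the correlations (dose–response) between ln rMSSD, HR, and SPE". A normality check decides between a parametric and a rank coefficient. The size bands given there include "0.1–0.3 small, 0.3–0.5 moderate, 0.5–0.7 large, 0.7–0.9 very large".
- **Primary outcome, first condition:** "For the monitoring to be considered successful, two of the three monitoring tools must yield significant results". The tools are SPE, HR and HRV.
- **Primary outcome, second condition**, added to the first: "the correlation between SPE and HR should be moderate to high so that they can be used in clinical practice".
- **Statistical analysis, weekly comparison:** "To analyze weekly differences in training loads using the SPE, HR, and HRV indices", done over the 12 weeks by magnitude-based inference.
- **Statistical analysis, ROC:** "The cutoff points for load increments with the HRV indices and SPE were obtained from the receiver operating characteristic curve". Accuracy measures are to be given for each Pilates level. HR is not named.
- **Pilates exercises**, on how the schedule was built: "We considered the degree of difficulty of each exercise as well as the dependence between volume and intensity". Study design adds that every man in the Pilates group passes through three levels in 36 sessions.

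**The concern.** A dose–response analysis needs a dose. Here the design supplies one: three graded levels and a schedule built on difficulty, volume and intensity. None of it is a variable in the correlations. ln rMSSD, HR and SPE are all recorded on the participant as reactions to a session, and a correlation between two reactions says only that they move together. They can do so because of training load, or because of anything else that affects both, such as fatigue or poor sleep on the day.

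This matters because the Background section's hypothesis is that the tools are useful for monitoring the progression of Pilates loads, and the Discussion expects the results to guide prescription. If the criterion for use in practice can be met by a tool that does not follow progression, a recommendation of that tool has no support on the point that counts.

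**Working it through.** The plan gives no figure on this point to reproduce. The check is a reading of the criterion followed by an illustration.

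**Step 1. Which combinations pass the Primary outcome rule?** Two of {SPE, HR, HRV} must be significant, and the SPE–HR correlation must be at least moderate.

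| Tools with a significant result | Two-of-three met? | Tool supported only by the correlation |
|---|---|---|
| SPE, HR (with or without HRV) | yes | none |
| SPE, HRV | yes | HR |
| HR, HRV | yes | SPE |
| HRV only, or none | no | – |

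Any passing pair includes SPE or HR, so both cannot fail. In rows two and three, however, one of them is endorsed without a positive result of its own. Row two is the more exposed, because the ROC analysis at least examines SPE against level but leaves HR out.

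**Step 2. Can row two occur with a correlation that passes?** From the documents: 27 men per group, 36 sessions, three levels, moderate starting at 0.3. Assumed: 12 sessions per level; residual SD 1 for each tool; SPE rises 0.5 SD per level; HR has no level effect; a share s = 0.5 of the residual variance is common to both; sessions pooled.

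- Variance of level scored 0, 1, 2 in equal thirds: 2/3.
- Variance of SPE: 1 + 0.5² × 2/3 = 1.167. Variance of HR: 1.
- Covariance: s = 0.5.
- r = 0.5 / √(1.167 × 1) = 0.5 / 1.080 = **0.46**, inside the moderate band.
- AUC, advanced versus basic. SPE: shift 2 × 0.5 = 1 SD, so Φ(1/√2) = Φ(0.707) = **0.76**. HR: shift 0, so Φ(0) = **0.50**.

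In 500 simulated trials of 27 × 36 sessions under these assumptions, r averaged 0.46 and was at least 0.3 in all 500. Mean AUCs were 0.76 and 0.50.

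**Step 3. Dependence on the assumed share**, with r = s / 1.080:

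| s | 0.3 | 0.4 | 0.5 | 0.6 | 0.7 |
|---|---|---|---|---|---|
| r | 0.28 | 0.37 | 0.46 | 0.56 | 0.65 |

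The expected correlation reaches 0.3 once s is at least 0.3 × 1.080 = 0.32. HR's AUC is 0.50 throughout.

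**Step 4. The converse.** Let both tools rise 0.5 SD per level and share nothing else. Then r = 0.167 / 1.167 = 0.14. In 600 simulated trials, with half the residual variance between men, r reached 0.3 in 4%, while the AUC for advanced versus all other sessions was 0.70 for both tools. The correlation can therefore also fail two tools that do follow level.

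**The case against.** A reader might infer that SPE and HR could both be recommended although neither follows the training load. The documents do not support that. The correlation is added to the two-of-three rule, and any two of the three tools include SPE or HR. If neither responded to load, the joint rule could pass only through a false positive. With one 5% test per tool (an assumption, since the protocol does not define a significant result here), that is at most 5% + 5% = 10% of trials.

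Nor is it right that the plan as a whole has no evidence on load. The weekly analysis covers SPE, HR and HRV over the weeks in which the levels advance, and the ROC analysis relates SPE and the HRV indices to level.

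It can also be argued that a dose is present in another sense: the Primary outcome section defines session SPE times minutes, and TRIMP from HR, as internal load, so relating these to ln rMSSD could be read as internal load against autonomic response. That reading is possible but not secured. The correlation sentence names SPE and HR, not the load scores, and rMSSD is itself listed as a load tool. For the SPE–HR pair, which carries the clinical-use condition, both sides are load measures and neither is a response to the other.

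Finally, the size of the simulated correlation largely returns the assumed shared variance, and it is an assumption that graded exercise leaves HR unchanged. That is fair. The numbers show that the gap is possible, not that it is likely. If the tools are correlated only between men (between-person correlation 0.6, half the variance between persons, no level effect), the mean pooled correlation is 0.28 and 0.3 is reached in 43% of runs.

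What survives is that the weekly HR result is planned but nothing in the criterion requires it to be positive.

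**Conclusion.** The point holds in a limited form. The dose–response label is not earned, because no level, week or scheduled volume enters the correlations. The SPE–HR correlation measures agreement, not validity against load. Under the full rule one of the two tools, most plausibly HR, can be endorsed for practice on correlation alone when the other tool and HRV meet the two-of-three condition.

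In the illustration this gives r of about 0.46 with an AUC of 0.76 for SPE and 0.50 for HR. It rests on the assumed level effects, an equal split of sessions across levels and a shared residual variance of one half; a share of about 0.32 or more is enough for the expected correlation to reach moderate. The criterion should be changed, but the weekly and ROC analyses mean that the plan is not without evidence on progression.

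**What to change.** 1. Drop the dose–response label. Report the SPE, HR and ln rMSSD correlations, computed within person, as agreement between measures.
2. Add HR to the ROC analysis by Pilates level.
3. For each tool, fit a repeated-measures model of the session value on Pilates level (or week), with man as the clustering unit.
4. Reword the clinical-use criterion so that SPE and HR must each show its own association with level before that tool is declared usable. Keep the SPE–HR correlation as supporting information.

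This uses data that the trial already collects and costs one extra model per tool and some rewording. The downside is that SPE or HR may fail a criterion that it would otherwise have passed.

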## Methods/design

### Study design

A parallel randomized clinical trial is being conducted at the Center for Studies and Assistance in Physiotherapy and Rehabilitation of the Universidade Estadual Paulista (FCT/UNESP), Presidente Prudente, São Paulo, Brazil. The trial was registered at ClinicalTrials.gov (NCT03232866) and approved by the research ethics committee of FCT/UNESP (protocol 061942/2017). The study protocol follows the SPIRIT 2013 checklist (Standard Protocol Items: Recommendations for International Trials) [12] (Additional file 3) and TIDieR (Template for Intervention Description and Replication) [13], indicating that information about and the quality of the reports of the interventions are well described [14]. Prior to participation, the volunteers received oral and written instructions and signed a consent form agreeing to participate in the study. All personal data will remain confidential. Note that, although very unlikely, participants who suffer any kind of injury as a result of participation will receive a free medical evaluation and physiotherapy treatment.

Participants were divided into two groups: the Pilates group and the control group. Participants in the Pilates group underwent 12 weeks of Pilates exercises for three times a week, for a total of 36 sessions. Each session lasted for approximately 60 min. During this training period, participants were required to pass through the three levels of the Pilates method: basic, intermediate, and advanced. The control group were asked to maintain their current level of daily activities without taking any type of exercise training. A flowchart for the study and group composition are shown in Fig. 1.

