### Secondary outcomes

The HRV will be calculated from the series of RR intervals captured by the cardiofrequency monitor using linear methods. It will be analyzed in the time and frequency domains. A Poincaré plot will be used. All HRV indices will be calculated by Kubios HRV software version 3.1.0.

The RR interval series was recorded before and after the 12 weeks of training. There were 1000 RR intervals in each data set. In addition, daily tracking of each session will be analyzed. Stretches of 256 consecutive RR intervals were recorded every 5 minutes. In both analyses, the most stable stretches were used to avoid any bias in the analysis and data interpretation [5]. The time series of RR intervals will undergo moderate digital filtering using Kubios, supplemented by manual filtering to eliminate premature ectopic beats and artifacts. Only series with more than 95% of sinus beats will be included in the final analysis [23].

The time domain (rMSSD and standard deviation of all RR intervals) [24], frequency (low and high) [23, 25, 26], and Poincaré plot (standard deviation of data from *x* = *y* and standard deviation of data from the line orthogonal to *x* = *y* that passes through the mean value of the data) [23, 27, 28] HRV indices will be used for the analyses before and after the 12 weeks of training. Only the time domain indices and the Poincaré plot will be used for daily tracking.

HR [23], respiratory rate measurements [29], and oxygen saturation [30] were captured. Blood pressure [31] was measured. A subjective pain assessment was obtained through a visual analog pain scale [32, 33]. Volunteers were asked to fill out a psychometric questionnaire [17] before and after the training period, as well as before all training sessions.

All these outcomes were collected in the initial evaluation and in the final evaluation after the 12 weeks of training, in addition to before and after each Pilates session. Table 1 lists outcome collection time points.

**Table 1 Tab1:** Time points for outcomes

Outcomes			Time point				
			Initial assessment	Final evaluation	During the sessions		
					Before and at the end	Every 5 min	15 min after
Primary	Load monitoring	Borg			X	X	X
		HR			X	X	X
		rMSSDmean			X	X	
		rMSSDcv			X	X	
Secondary	ANS	HRV	X	X	X	X	
	Cardiorespiratory metrics	BP	X	X	X		
		HR	X	X	X		
		*f*	X	X	X		
		SatO_2_	X	X	X		
	Pain	VAS	X	X	X		
	SPE	Borg	X	X			

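### The rule that calls an AUC of 0.65 or more significant is a discrimination threshold with no error rate, and the cut-offs drawn from the same curves will look more accurate than they are

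*Protocol article*

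**What the plan says.** Under Statistical analysis, the Protocol article sets out the ROC work in four steps.

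- Source of the cut-offs: "The cutoff points for load increments with the HRV indices and SPE were obtained from the receiver operating characteristic curve".
- Their accuracy: "The sensitivity, specificity, positive predictive value, and negative predictive value for each level of the Pilates method will also be calculated".
- The criterion: "The area under the curve will be considered significant when values ≥0.65 are obtained". A citation is given, but no null hypothesis, p-value or interval.
- The choice of index: "a comparison will be made between the receiver operating characteristic curves of each HRV index to detect the most representative" for internal training load.

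The same section sets p < 0.05 for the comparisons between groups.

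The structure of the data is given elsewhere. Study design says "Participants in the Pilates group underwent 12 weeks of Pilates exercises for three times a week, for a total of 36 sessions" and that "participants were required to pass through the three levels of the Pilates method: basic, intermediate, and advanced". Secondary outcomes adds "Stretches of 256 consecutive RR intervals were recorded every 5 minutes". According to the study outline, controls had only the initial and final evaluations, so session data exist for the Pilates arm alone.

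**The concern.** Whether an AUC of 0.65 is evidence against chance depends on how many observations lie behind it and how they are correlated. A fixed value has no error rate until those are known, and the article gives neither. The word significant therefore means one thing for the group comparisons and another for the ROC curves.

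The second problem is that one set of curves serves to choose the cut-offs, describe their accuracy and pick the preferred index. A cut-off is chosen because it performs well in the data at hand, so its accuracy in those data flatters it.

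The Discussion says that the results can guide practitioners in prescribing the method. The cut-offs for raising the load are the part they would use most directly.

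**Working it through.** **Inputs.** The Sample size calculation gives 27 men in the Pilates arm. Study design gives 36 sessions per man and three levels. The 0.65 rule comes from Statistical analysis. Assumed, because the article does not say: the curves separate two adjacent levels, sessions are spread equally (36/3 = 12 per level, or 4 weeks), and the data are normal.

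**The plan's own figure.** The 0.65 has no stated derivation to reproduce. The sample size does reproduce: 2 × (1.960 + 0.842)² × (23.94/19.02)² = 24.87, rounded up to 25 per group. Adding 10% gives 27.5, against the stated 27.

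**What an AUC of 0.65 means under different units of analysis.** Under no discrimination, with independent values, SE₀ = √[(n₁ + n₂ + 1)/(12 n₁n₂)]. For 27 v 27 this is √(55/8748) = 0.0793, so z = 0.15/0.0793 = 1.89.

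| Values compared | SE₀ | Two-sided p at 0.65 | AUC needed for p < 0.05 |
|---|---|---|---|
| 27 v 27 (one per man per level) | 0.0793 | 0.059 | 0.655 |
| 108 v 108 (weekly, pooled as independent) | 0.0394 | 0.00014 | 0.577 |
| 324 v 324 (sessions, pooled as independent) | 0.0227 | 4 × 10⁻¹¹ | 0.544 |

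The Hanley–McNeil standard error at A = 0.65, 27 v 27, uses Q₁ = A/(2 − A) = 0.4815 and Q₂ = 2A²/(1 + A) = 0.5121:

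SE = √{[0.2275 + 26(0.4815 − 0.4225) + 26(0.5121 − 0.4225)]/729} = 0.075

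The 95% interval is 0.65 ± 1.96 × 0.075, or 0.503 to 0.797.

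The two sets of 27 values come from the same men, so independence is only a reference case. In simulations with a 30–50% share of variance between men, the null SD of the AUC was 0.061 to 0.066. Then z = 0.15/0.0607 = 2.47 to 0.15/0.0663 = 2.26, and p is about 0.013 to 0.024. The same 0.65 falls on either side of 5% depending on a correlation that the article does not give.

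**Optimism of the cut-offs.** The simulation used 27 men, two levels and 1,000 runs per scenario, with a shift of 0.545 SD, so that the true AUC is Φ(0.545/√2) = 0.65. The best possible Youden index is then 2Φ(0.545/2) − 1 = 0.21. The cut-off that maximised the index was judged on its own data and against the population.

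| Values per man per level | Apparent Youden | True Youden | Overstatement |
|---|---|---|---|
| 1 | 0.32 | 0.19 | 0.13 |
| 4 | 0.27 | 0.20 | 0.07 |
| 12 | 0.24 | 0.21 | 0.03 |

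These are for one marker with independent values. Introducing correlation within men hardly changed them. Choosing among several indices would add to them.

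**Clustering.** This is a naive 5% test of AUC = 0.5 with 12 values per man per level. Variance shares are assumed.

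| Between-man pattern | Type I error | Coverage of naive 95% interval |
|---|---|---|
| Overall level only (50% of variance) | about 1% | 0.99 |
| Overall level 40%, man-by-level 10% | 14% | 0.86 |
| Overall level 30%, man-by-level 30% | 32% | 0.68 |

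**Redundant index.** Secondary outcomes lists both rMSSD and the Poincaré spread about x = y (SD1). SD1 equals rMSSD/√2 to negligible error, and an AUC is unchanged by rescaling or by logs, so the two curves are the same.

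**The case against.** The strongest objection is that the article is condensed. The ROC unit, clustered intervals and internal validation are details that a full protocol or analysis plan commonly holds, and 0.65 may be meant as a minimum useful size. A good deal of this stands, and it rules out several stronger readings.

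- **That the plan treats sessions as independent.** A reader might infer this from the repeated sessions, but the article nowhere says so. It is silent on the unit of analysis.
- **That clustering flatters the results.** Each man contributes to every level, so a naive test may be conservative or too liberal. Clustering distorts intervals and curve comparisons; it does not by itself raise the AUC that is set against 0.65.
- **That useless markers will often pass.** Pure noise reached 0.65 in at most about 3.5% of simulated runs with one independent value per man per level (upward direction), and in 0.4% or fewer at session level. Multiplying a false-positive rate over several indices as if they were independent is not warranted, since the article does not fix their number and they overlap.
- **That leaving HR out of the ROC sentence is an error.** HR is analysed by zone scores, weekly inference and correlation, and no HR cut-off is promised. Adding it is a preference.
- **That SD1 is certainly compared with rMSSD.** The load-monitoring set named under Statistical analysis is the weekly rMSSD and its coefficient of variation. The redundancy matters only if the Poincaré indices enter.

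The objection does not remove the stated rule. The article itself attaches the word significant to a fixed AUC, and it describes no second data set for the cut-offs.

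**Conclusion.** The point holds in this limited form. The 0.65 rule is a threshold for discrimination that is labelled as a significance criterion. Its p-value runs from about 0.06 (27 v 27, independent) to 4 × 10⁻¹¹ (324 v 324, independent), so the label carries no fixed error rate.

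Same-data accuracy will be overstated by about 0.03 to 0.13 on the Youden scale for one marker at a true AUC of 0.65: small if many sessions per man are used, material if the analysis is per man. Intervals and curve comparisons that overlook the repeated sessions could be wrong in either direction; this is a risk left open by the text, not a stated error.

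These sizes rest on normal data, equal numbers per level and assumed variance shares. They also rest on reading the cut-offs as derived from this trial. The sentence on cut-offs is in the past tense, but no other source is described.

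A reader might also suppose that the AUC rule decides the primary requirement that two of the three monitoring tools give significant results. The article does not make that link, and nothing here depends on it.

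**What to change.** 1. Call 0.65 a minimum discrimination threshold, and require in addition that the lower 95% limit of the AUC exceeds 0.5. Keep both conditions: with many sessions the lower limit alone would be more lenient, since an AUC of about 0.544 would pass at 324 v 324 if independent.
2. State the unit of analysis of the ROC curves, and obtain AUC intervals and curve comparisons by bootstrap over men, keeping all of a man's sessions together.
3. Report sensitivity, specificity and predictive values from leave-one-man-out cross-validation, with the cut-off and the choice of index repeated each time a man is left out. Label any same-data figures as apparent.
4. If the Poincaré indices are compared, do not count SD1 as separate evidence from rMSSD.

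The cost is some analysis outside MedCalc, and intervals that may be wider with slightly lower reported accuracy. No new data are needed.

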### Participants

A total of 54 healthy male volunteers were recruited from the local university (UNESP) through pamphlets, online media, personal invitations, telephone calls, and SMS messages. These procedures were recommended by Treweek et al. [15] as strategies to improve participant recruitment.

The inclusion criteria were: male; 18 to 35 years of age; healthy (self-report); not having practiced Pilates prior to the study; not a smoker or an alcoholic; not presenting with a metabolic, cardiac, or endocrine disorder; with no arrhythmia; not using drugs that influence the autonomic modulation of the heart; and without physical limitations such as musculoskeletal, inflammatory, or neurological diseases that would prevent them from doing Pilates.

Individuals who suffered from a musculoskeletal injury during training, those who attended less than 85% of training sessions, those who failed to progress between the three levels of the Pilates method, those who were unable to respond adequately to subjective scales, and those with errors in the captured RR intervals were excluded from the study. Participants were instructed to maintain their daily dietary routine, to abstain from taking anti-inflammatory medications and analgesics, and not to perform any other type of exercise during the intervention period. These requests were reinforced during the training period and monitored by self-report [16].

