### Sample size calculation

The sample calculation was carried out based on Barbosa et al*.* [34] with the rMSSD index. The clinically relevant difference was 19,02 ms and the standard deviation 23,94 ms. For a two-tailed hypothesis test, the significance level for the sample calculation was 5% and the power of the test was 80%. The sample size was calculated to be 25 per group. To account for withdrawals, the sample size was increased by 10% to give 27 volunteers per group.

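### Filling absent outcomes with the group's worst value does not secure power; it costs power when loss is equal and biases the between-group difference when loss is unequal

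*Protocol article*

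**What the plan says.** The last paragraph of the Statistical analysis section defines the analysis set: "All participants included in the initial assessment will be considered under the intention-to-treat approach". The same sentence adds that "the worst outcome obtained by the study group will be selected to ensure the power of the data analysis". It does not use the word *missing*, but in an intention-to-treat sentence the only plausible reading is that an absent outcome is replaced by the worst one observed. The article states no other rule for absent outcomes. The Discussion lists the intention-to-treat analysis as a strength.

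The same section sets the between-group test: "In the comparison between the groups, the unpaired *t* test or Mann–Whitney test will be used depending on the normality of the data", at p < 0.05.

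The Sample size calculation section has already allowed for losses: "To account for withdrawals, the sample size was increased by 10% to give 27 volunteers per group".

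The Participants section excludes, after entry, men injured during training and "those who attended less than 85% of training sessions, those who failed to progress between the three levels of the Pilates method". The control group has no sessions, only the initial and final evaluations.

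**The concern.** Single-value filling treats an invented observation as a measured one. If that value is the extreme of the sample, two things follow. The SD rises, which works against power. The mean of the arm being filled moves towards the bad end, and if the two arms are not filled equally the difference moves with it.

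Unequal filling is likely in this design. The attendance and progression exclusions, and injury during training, can arise only in the Pilates arm. If those men are kept by intention to treat and given the worst value, the Pilates mean is lowered for a reason the control arm does not share.

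The rule is also not fully specified. *Study group* could mean the man's own arm, the Pilates arm or all participants. *Worst* has no stated direction for outcomes such as low- and high-frequency power or respiratory rate. The analyst would have to choose both.

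At stake is the randomized comparison of the initial/final outcomes, including rMSSD, the variable on which the trial was sized.

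**Working it through.** **Inputs.** From Sample size calculation: difference 19.02 ms, SD 23.94 ms, two-sided 5%, 80% power, 25 per group raised to 27. From Statistical analysis: unpaired t test. Assumed, because the article does not state them: 0 to 5 of 27 missing per arm, missing at random, normal outcomes, higher rMSSD better. Three of 27 (11%) is close to the plan's 10% allowance. Five in one arm is a stress case beyond it.

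**Step 1. The plan's figure.** n per group = 2 × [SD × (1.960 + 0.842) / difference]² = 2 × [23.94 × 2.802 / 19.02]² = 24.9, rounded up to 25. This reproduces "The sample size was calculated to be 25 per group". With all 27 per arm observed, the t test has 82% power.

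**Step 2. Bias under own-arm filling.** If m of 27 men are filled with the minimum of the other 27 − m, the arm mean shifts on average by (m/27) × E[min] × SD, where E[min] is the expected minimum of 27 − m standard normal values.
- m = 1: (1/27) × (−1.982) × 23.94 = −1.76 ms
- m = 3: (3/27) × (−1.948) × 23.94 = −5.18 ms
- m = 5: (5/27) × (−1.910) × 23.94 = −8.47 ms

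Loss in Pilates only therefore gives 19.02 − 1.76 = 17.3, 19.02 − 5.18 = 13.8 and 19.02 − 8.47 = 10.6 ms. Three lost in control only gives 19.02 + 5.18 = 24.2 ms. Equal loss cancels.

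**Step 3. Power.** Simulation with unpaired t tests, 40,000 to 100,000 runs per scenario. The column for observed values only is the exact t-test power.

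| Missing, Pilates / control | Power, observed only | Own-arm worst: difference, power | Pooled worst: difference, power |
|---|---|---|---|
| 1 / 1 | 80% | 19.0 ms, 78% | 18.4 ms, 74% |
| 3 / 3 | 77% | 19.0 ms, 72% | 16.9 ms, 56% |
| 1 / 0 | 81% | 17.3 ms, 72% | 16.5 ms, 66% |
| 2 / 1 | 79% | 17.3 ms, 68% | 15.8 ms, 56% |
| 3 / 0 | 79% | 13.8 ms, 49% | 11.5 ms, 28% |
| 5 / 0 | 77% | 10.6 ms, 32% | 6.5 ms, 6% |
| 0 / 3 | 79% | 24.2 ms, 93% | 24.3 ms, 94% |

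With three missing per arm, the average SD in the Pilates arm rises from 23.9 to about 27 ms (own-arm) or 31 ms (pooled). That is where the power goes when loss is equal.

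**Step 4. No true effect, own-arm filling.** Three missing in one arm give about 10% two-sided type I error instead of 5%, nearly all of it against the arm with the losses. Five missing in Pilates give about 20%. One missing in Pilates gives about 5%, and equal loss gives no inflation beyond simulation error.

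**Step 5. Mann–Whitney instead of t, own-arm filling.** Three missing per arm: 75% on observed values, 69% filled. Three missing in Pilates only: 76% against 47%. The rank test does not rescue the rule.

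**The case against.** The strongest reply is that the harm depends on losses the article does not report. Trial status says that all participants are attending, and the plan allows for only 10% loss. With one missing per arm the cost is about two points of power, and with two missing in Pilates and one in control there is no type I inflation. This stands: the counts are assumptions, and the small-loss end is mild when loss is balanced. It does not save the rule. Attendance alone does not exclude later exclusions or unusable RR series, and one missing Pilates man already takes power from 81% to 72%.

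Three stronger readings are tempting and not supported.

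- A reader might infer that the rule always biases the difference and always cuts power. With equal loss and own-arm filling the difference is unbiased, and with loss in control only the rejection rate rises.
- A reader might infer that the rule decides the sign of the result. At the planned effect the average estimate stays positive in every scenario above. Only with no true effect do the losses set the direction.
- A reader might infer that the primary outcome is distorted in the same way. Training load is measured only during sessions, hence only in the Pilates arm. It has no between-group comparison, and the article does not say whether the rule covers missed sessions.

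It could also be said that worst-value filling is deliberately conservative. The article gives a different reason, and the control-loss scenario shows that it need not be conservative.

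**Conclusion.** The point holds in conditional form. The stated rationale is wrong: in no scenario does filling bring back the power that missing men take away. With equal loss the cost is moderate: 77% falls to 72% (own-arm) or 56% (pooled) at three per arm, and the pooled reading also makes the difference about 2 ms too small. With loss only in Pilates, which the arm-specific exclusions make plausible, three missing men remove about 5 of the 19 ms and 30 points of power (79% to 49%). With loss only in control, the higher rejection rate is an artefact of an inflated difference, with about 10% false benefit under no effect.

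These sizes rest on the plan's difference and SD, normal outcomes, loss at random and an assumed 0 to 5 missing of 27 per arm. They apply to the initial/final between-group comparisons. Reading *study group* as the Pilates arm alone was not computed. The unclear reference group is a defect in itself: with three missing in Pilates, the choice between own-arm and pooled moves power from 49% to 28%.

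**What to change.** For the initial/final outcomes, make the main analysis one of all randomized men by a likelihood-based mixed model, or by multiple imputation within arm with the baseline value as predictor. Attendance can be added as a predictor in the Pilates arm only, since the control arm attends no sessions. These are standard choices and not the only acceptable ones.

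Keep worst-value filling, if wanted, as a sensitivity analysis, limited to outcomes with a clear bad direction and with the reference group named. Say whether any such rule applies to missed sessions in the training-load analysis. Delete the claim that the rule secures power, and report the number missing by arm with reasons.

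The cost is a change of analysis wording and slightly more analysis work. No new data are needed.
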